## Background

Fractures of the humeral diaphysis (humeral shaft fractures) constitute 1.2% of adult fractures in the UK, with an overall incidence of 12.9 per 100,000 per year [1]. These injuries are more common in women and have a bimodal age distribution, with peaks of prevalence occurring in younger adults following high-energy trauma and older adults following low-energy trauma [1–3].

Humeral shaft fractures are routinely managed non-operatively, with the widespread use of a prefabricated humeral brace, as first described by Sarmiento et al*.* in 1977 [4]. The purported benefits of this technique (over conventional plaster immobilisation) include rapid and uninterrupted osteogenesis and early mobilisation of the shoulder and elbow, thus enhancing functional outcomes [4]. Subsequent studies comparing bracing with plaster immobilisation have demonstrated faster fracture union, reduced rates of varus mal-alignment and confirmed functional advantages in terms of shoulder and elbow mobility [5, 6].

Although functional bracing has resulted in low rates of humeral shaft fracture nonunion in some series [7–9], others have reported nonunion rates of 10% or more [10–13], with the highest rate reported as 33% [14]. When fracture union does occur, the reported time to union ranges from 7.5 to 11.5 weeks [7, 9], during which time almost all activities of daily living are restricted, and there is a risk of skin breakdown and secondary cellulitis that can necessitate brace removal [13]. Moreover, while malunion is considered to be tolerated well by patients, the acceptable thresholds are based upon an historic series of just 32 patients, who were examined by a single author [15]. A more recent series has suggested that malunion and consequent loss of shoulder range of motion can occur in up to 38% of patients treated with a brace [16].

The perceived limitations of humeral bracing have brought about a gradually increasing role for operative fixation [17]. Although intramedullary nailing is considered feasible, published case series [18], reviews [19, 20] and randomised controlled trials [21, 22] have consistently recommended open reduction and internal fixation (ORIF) as the strategy of choice when surgery is indicated.

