### Secondary outcome measures

Secondary outcome measures will include:Change in the DASH score over the 1-year follow-up periodPain assessment, using a visual analogue scale (0 to 10)Complications of treatment, including neurovascular injury, superficial or deep infection, failure of fixation, revision surgery, skin complications (including eczema and cellulitis) and complex regional pain syndromeTime to return to work and sports (if relevant)Satisfaction with the service, using a visual analogue scale (0 to 100), and with the appearance of the affected limb, also using a visual analogue scale (0 to 10)Range of motion at the shoulder and elbowRadiographic assessment, using standard anteroposterior and lateral radiographs of the humerus to assess the progression of fracture healing (union or nonunion) and final humeral deformity (malunion)EuroQol (EQ-5D) health outcome score [30]12-item Short Form (SF-12) health survey score [31]Health economic analysis

Outcome measures 1 to 9 have been collated into a single data collection form (one form per study participant).

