### Power calculation and statistical analysis

Prior to study commencement, a prospective power calculation was used to determine the number of patients required in each treatment group. The minimal clinically important difference in the DASH score is reported to be 10 points [32], and the assumed standard deviation is 12 points for both the operative and non-operative groups [33]. Thus, using a two-sided *t*-test with 5% significance, a total of 70 patients (35 in each group) are required to produce a 90% power to detect a meaningful difference (in terms of the DASH score at 3 months post-intervention) between the two groups, assuming a 10% loss to follow-up.

Data will be analysed on an intention-to-treat basis. Data analysis will be performed by a senior statistician, employed by the local clinical research facility and independent of the study team. The primary outcome measure (DASH score at 3 months post-intervention) will be compared between the two treatment arms, using a two-sided independent samples *t*-test or non-parametric equivalent (as indicated by the normality of the data). This method will also be used to compare the other continuous outcome measures between the two treatment arms (e.g. pain score, satisfaction scores, shoulder and elbow range of motion, EQ-5D score and SF-12 score). The pattern of change in continuous outcome measures over the study period will be presented graphically, broken down by treatment allocation. A linear regression model will be generated for each participant by plotting the DASH score from 6 weeks to 1 year post-intervention and the gradient of the regression line (i.e. the rate of change in the score) will be compared between treatment groups. Multivariate linear regression, including analysis of covariance (ANCOVA), will also be used to adjust for the potential effect of pre-injury DASH score, age and other prognostic factors affecting the DASH score. Binary outcomes (e.g. treatment complications, re-operation and nonunion or malunion) will be compared between the two treatment arms using a binomial test for the comparison of proportions. Two-tailed *p* values will be reported where possible, and statistical significance will be set at *p* = 0.05.

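### The only stated comparison of final humeral deformity is malunion yes/no, although the protocol calls the accepted malunion thresholds weakly founded; angulation in degrees should be compared as well

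*Protocol article*

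**What the plan says.** Three parts of the protocol article bear on this.

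- **Secondary outcome measures.** The radiographic item uses standard anteroposterior and lateral views to assess healing and "final humeral deformity (malunion", where the bracket then closes. Deformity is thus identified with a category. No angle, plane or unit is given.
- **Power calculation and statistical analysis.** "Binary outcomes (e.g. treatment complications, re-operation and nonunion or malunion) will be compared between the two treatment arms" by a binomial test for proportions. Continuous outcomes go to a t-test or its non-parametric equivalent: "This method will also be used to compare the other continuous outcome measures between the two treatment arms (e.g. pain score", followed by satisfaction, range of motion, EQ-5D and SF-12. Angulation is not in that list, but the list is open.
- **Background.** On malunion, "the acceptable thresholds are based upon an historic series of just 32 patients, who were examined by a single author". The same paragraph says that malunion with loss of shoulder motion "can occur in up to 38% of patients treated with a brace". That is the only malunion rate in the article.

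**The concern.** A yes/no malunion variable needs a threshold. The one comparison of deformity that the plan commits to therefore takes a form whose accepted thresholds the authors themselves describe as resting on little. Two consequences follow.

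First, whether the arms differ can depend on where the line is drawn, so a finding of more, or no more, malunion is partly a finding about the threshold. The Discussion says that assessors cannot be blinded, which makes it more important that the line is drawn before the data are seen.

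Second, reducing an angle to a category costs power in a trial with about 31 or 32 evaluable patients per arm. Alignment is a contrast the article itself expects: the Background quotes the brace figure above, and the Discussion cites a retrospective comparison with more malunion after bracing. A real difference in alignment could go undetected when the same radiographs would have shown it.

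**Working it through.** **1. The plan's own figure.** Inputs from the statistical section: difference 10 DASH points, SD 12, two-sided 5%, power 90%, 10% loss.

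n per arm = 2 × (1.960 + 1.282)² × 12² / 10² = 30.3, so 31; 31 / 0.9 = 34.4, so 35 per arm and 70 in total. The stated size reproduces. (The exact t-test needs 31.25, so 32 per arm, or 36 after loss; the difference is immaterial.) It concerns the DASH score only. No power is stated for deformity. After 10% loss, 35 × 0.9 = 31.5 patients per arm remain.

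**2. Efficiency kept by a yes/no split.** Assume a normally distributed deformity measure with a shift between arms. Relative to a comparison of means, a split at pooled prevalence p keeps φ(z_p)² / [p(1 − p)] of the information, where φ is the standard normal density and z_p the normal quantile. At p = 0.38: z = −0.305, φ = 0.381, and 0.381² / (0.38 × 0.62) = 0.62.

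| Pooled malunion prevalence | Efficiency kept | Lost |
|---|---|---|
| 50% | 64% | 36% |
| 38% | 62% | 38% |
| 25% | 54% | 46% |
| 20% | 49% | 51% |
| 10% | 34% | 66% |

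The prevalence here pools both arms, whereas the 38% in the Background is an upper figure for braced patients. If malunion after plating were near zero (an assumption), the pooled figure would be about 38% / 2 = 19%, and 48% would be kept.

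**3. Power with 31 analysed per arm.** Two shifts are assumed: 0.83 SD (the ratio 10/12 that the plan uses for DASH, borrowed only as a benchmark) and 0.5 SD. The operative rate is Φ(z_brace − shift). For example, with 38% in the brace arm and 0.83 SD, Φ(−0.305 − 0.83) = 12.8%. The pooled rate is then 25.4%, and the normal-approximation power is Φ[(0.252 − 1.96 × 0.1106) / 0.1058] = 63%. The article does not say which binomial test is meant, so Fisher's exact test is shown too.

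| Shift | Brace malunion | Operative malunion | Power, continuous | Power, proportions | Power, Fisher |
|---|---|---|---|---|---|
| 0.83 SD | 38% | 12.8% | 90% | 63% | 54% |
| 0.83 SD | 20% | 4.7% | 90% | 45% | 27% |
| 0.83 SD | 10% | 1.7% | 90% | 28% | 5% |
| 0.5 SD | 38% | 21% | 49% | 31% | 23% |
| 0.5 SD | 20% | 9% | 49% | 23% | 13% |
| 0.5 SD | 10% | 3.7% | 49% | 16% | 3% |

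**4. Illustration in degrees.** Simulation of 20,000 trials with 32 per arm and an assumed brace mean of 14 degrees, SD 8; t-test on degrees against a two-proportion test at three arbitrary cut-offs.

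| Assumed operative arm | Degrees | Cut 15 | Cut 20 | Cut 30 |
|---|---|---|---|---|
| Mean 9, SD 8 | 69% | 48% | 36% | 1% |
| Mean 4, SD 8 | 99.9% | 93% | 79% | 1% |
| Mean 5, SD 4 | about 100% | about 100% | 95% | 1% |

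The 30-degree column implies only about 2% malunion with a brace, far below the one rate the article quotes, and should carry little weight. In no cell does the split gain power; how much it loses depends on the assumed inputs and on the cut-off.

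**The case against.** The case against is a serious one, and several parts of it stand.

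- **No cut-off is stated.** A reader might infer that the trial will apply the very thresholds the Background criticises, or that they are angular. The article says neither. The criticism is background on bracing, and the definition of malunion may properly sit in the full protocol, the analysis plan or the data collection form. Its absence here is no fault.
- **Angles may not be recorded.** Nothing says that deformity is read in degrees, so the plan cannot be accused of throwing away a quantity it has measured.
- **The continuous list is open.** It is introduced as examples, so a comparison of angles is not excluded. A reader might conclude that malunion is the only comparison that will be made; the article supports only that it is the only one stated.
- **Most of the information is not necessarily lost.** That inference holds only at a pooled prevalence of about 20% or less. At 34% to 38% about 60% is kept.
- **Large differences survive the split.** In two of the three scenarios in degrees, power stays at 79% or more at the 15- and 20-degree cut-offs.

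What does not stand is the argument that all of this is detail left to another document. The article expressly assigns malunion to the binary comparison, which is a stated analysis choice. An open list of continuous outcomes does not commit anyone to analysing angulation.

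**Conclusion.** The point holds in a limited form. The only stated comparison of final deformity is malunion yes/no, in a protocol that itself calls the accepted thresholds weakly founded. Such a split makes the result depend on the threshold and loses power.

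The direction of the loss is general under the normal shift model. Its size is illustrative, because the article gives no angle mean, SD or cut-off: roughly 38% of the efficiency at a pooled prevalence of 38%, about half at 20%, and about two thirds at 10%.

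It would go too far to call the malunion result uninterpretable. Malunion rates are the terms in which the article discusses earlier studies, and they deserve reporting. Deformity is one part of one secondary outcome; the DASH comparison and the total of 70 are untouched. This is a cheap improvement.

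**What to change.** In the protocol or analysis plan:

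1. Record final angulation in degrees on the anteroposterior and on the lateral radiograph.
2. Name it as a continuous secondary outcome, compared between arms by the method already planned for such outcomes (t-test or non-parametric equivalent), and report the difference with a 95% confidence interval for each plane.
3. Keep the malunion proportion as a supporting result, at a threshold written down before outcome data are examined. Which threshold is a clinical matter for the investigators.

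The cost is a few sentences and the effort of writing down an angle from films already planned; no visits, radiographs or patients are added. The drawback is that a difference in degrees is clinically less familiar than a malunion rate, which is the reason to keep both.

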### Missing data

The study sample size has been increased to provide for up to 10% loss to follow-up at the primary outcome timepoint (3 months post-intervention). All clinical and outcome data will be collected in the outpatient clinic, where clinical reviews and radiographs (where required) are also performed. These appointments reflect routine follow-ups of a humeral shaft fracture in the study centre, and the investigators anticipate this arrangement will limit missing data considerably. The participant dropout rate for each treatment arm will be reported and compared. If the participant dropout rate at the primary outcome timepoint is substantial, a sensitivity analysis may be performed. Missing data at other timepoints will be accounted for by plotting a line of best fit for the data points for each participant and comparing the gradient of the regression line (i.e. the rate of change in the variable of interest) between treatment groups.

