### Outcome assessment

All follow-up assessments will take place during outpatient clinic visits at 2 weeks, 6 weeks, 3 months, 6 months and 1 year. At each clinic visit, a physical examination will be performed, complications noted and the need for any further surgery recorded. Patients will be given time to complete a self-reported questionnaire, which will generate clinical outcome scores. The 1-year follow-up will enable study investigators to assess whether any differences between the operative and non-operative groups (if any) are sustained for 1 year post-intervention and to detect any important complications that may occur within the first year (e.g. nonunion).

The Standard Protocol Items: Recommendations for Interventional Trials (SPIRIT) [27] checklist is given in Additional file 1. The SPIRIT schedule of enrolment, interventions and assessments is shown in Fig. 3.

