### Primary outcome measure

The primary outcome measure is the DASH score at 3 months post-intervention. The DASH score is a functional rating scale that was developed in 1996. It has been used extensively as a research tool in upper limb surgery [28]. It consists of a 30-item self-reported questionnaire, and two optional modules, one assessing work and the other sports and performing arts. Patient symptoms (including pain, weakness, stiffness and tingling or numbness) and functional status (including physical, social and psychological aspects) during the week prior to survey completion are assessed. The final score is from 0 to 100, with 0 representing no disability and 100 the worst possible disability. A recent study demonstrated the DASH score to be both valid and reliable in evaluating outcomes in patients following a humeral shaft fracture [29].

The null hypothesis is that there is *no*
*difference* in early functional outcomes (DASH score at 3 months post-intervention) between the operative and non-operative management of patients following a humeral shaft fracture.

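### A cheap improvement: the self-completed primary DASH is collected only at clinic visits, so a missed 3-month visit loses a score that needs no examination

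*Protocol article*

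**What the plan says.** All references are to the protocol article.

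- **Primary outcome measure:** "The primary outcome measure is the DASH score at 3 months post-intervention". Of the instrument it says: "It consists of a 30-item self-reported questionnaire".
- **Outcome assessment:** "All follow-up assessments will take place during outpatient clinic visits at 2 weeks, 6 weeks, 3 months, 6 months and 1 year". At those visits, "Patients will be given time to complete a self-reported questionnaire, which will generate clinical outcome scores".
- **Missing data:** "All clinical and outcome data will be collected in the outpatient clinic". The reason given is that the appointments are the centre's routine follow-up for this fracture, and "the investigators anticipate this arrangement will limit missing data considerably". Dropout is to be reported and compared by arm. For the primary timepoint, "If the participant dropout rate at the primary outcome timepoint is substantial, a sensitivity analysis may be performed". The line-of-best-fit method is for missing data at the other timepoints.
- **Power calculation and statistical analysis:** 35 patients per arm give 90% power for a 10-point difference with SD 12, after allowing 10% loss. The primary test is an unadjusted t-test or its non-parametric equivalent. ANCOVA is also planned, adjusting for pre-injury DASH, age and other prognostic factors that are not listed.
- **Exclusion criteria:** patients unable to return for the year of follow-up, or unable to comply with data gathering, are not enrolled.

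**The concern.** Examination and radiographs need the patient in the clinic; the DASH does not. Two sections nevertheless make attendance the only stated route for all outcome data, and the Missing data section presents that arrangement as the trial's protection against missing data. A patient who is willing to fill in the form but does not come at 3 months would have no primary outcome.

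Two things are at stake. The first is precision, because the sample size covers 10% loss and little more. The second is bias, if non-attendance is related to recovery and differs between arms. The trial is open-label and the arms have different follow-up needs, so this is possible, but the article gives no attendance figures.

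**Working it through.** **1. Reproduce the plan's sample size.** Inputs from Power calculation and statistical analysis: difference 10, SD 12, two-sided 5%, power 90%, loss 10%.

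n per arm = 2 × (1.960 + 1.282)² × 12² / 10² = 30.3, rounded up to 31. Then 31 / 0.90 = 34.4, rounded up to 35 per arm, 70 in total. This matches the plan. With the exact t-test the requirement is 32 per arm, or 36 after inflation (72 in total), two patients more. There is no sample-size error here.

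**2. Power by number of 3-month scores obtained.** Noncentral t with df = n1 + n2 − 2 and noncentrality 10 / (12 × √(1/n1 + 1/n2)). For 31 v 32 the noncentrality is 3.31 on 61 df, which gives 90.2%. Loss rates above 10% are assumptions.

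| Missed at 3 months | Scores available | Power | Power if half the missed scores are recovered |
|---|---|---|---|
| 0% | 70 | 93.0% | – |
| 10% | 63 | 90.2% | 91.5% (66 scores) |
| 15% | 59 | 88.2% | 90.7% (64) |
| 20% | 56 | 86.5% | 90.2% (63) |
| 30% | 49 | 81.5% | 88.2% (59) |

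The recovery rate of one half is also an assumption.

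**3. Bias of the complete-case comparison.** If a share m of one arm is missing, and those patients would have differed from the attenders by D points, the mean of the attenders is off by m × D. For example, 20% × 10 = 2 points. Both values are assumed.

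A simulation makes D follow from a mechanism. It uses 35 per arm, SD 12, and seven patients lost in total (7/70 = 10%, the plan's own allowance). Better 6-week DASH makes loss more likely in either arm, with the weight changing e-fold per SD. The correlation between the 6-week and 3-month DASH is 0.5 to 0.7.

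| Patients lost, one arm v the other | Bias in the 3-month difference (points) |
|---|---|
| 4 v 3 | 0.1 to 0.25 |
| 5 v 2 | 0.4 to 0.7 |
| 7 v 0 | 1.1 to 1.6 |

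The split between arms drives the result more than the correlation does. Even the extreme split gives 11% to 16% of the 10-point MCID (1.1/10 to 1.6/10).

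**4. Can analysis repair it?** In this simulation loss depends only on the 6-week DASH, which is observed. In the 7 v 0 setting, regression imputation on arm and 6-week DASH cut the bias to 0.05 points or less. The planned primary t-test does not use the 6-week DASH, and the ANCOVA does not name it as a covariate. If loss depended on the 3-month score itself beyond what the 6-week score predicts, no model could correct it reliably.

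**The case against.** The strongest reply is that the article says where data are normally collected and does not forbid rescheduling a non-attender or sending a form. Procedures for missed visits often sit in the full protocol, which is not shown. That stands in part: a fallback may exist. But both sections say that all assessments or data come from the clinic, so if there is a fallback their wording needs correcting.

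The plan also has real safeguards. The visits are routine care, patients unable to return are excluded, 10% loss at this timepoint is budgeted for, and dropout is compared by arm. These stand. They make missed visits rarer and visible, but they do not recover a missed score.

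Three stronger readings are tempting, and the documents support none of them:

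- **That the trial is underpowered.** Power of 90.2% at 10% loss is the design working as stated, and larger losses are assumed.
- **That attendance will differ by arm.** One might suppose that braced patients have more reason to attend and well-recovered patients less. No attendance data are given, and operated patients also have fixation and union to be checked.
- **That no analysis could repair the bias.** Where loss depends on the 6-week DASH, a model using that score removes it.

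Finally, remote completion mixes modes of completion in an unblinded trial. That is a small, real cost.

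**Conclusion.** This is a worthwhile, inexpensive improvement to the data-collection rule, not an error in the design or the sample size. As worded, the plan lets a missed 3-month visit remove a primary score that the instrument does not require to be lost.

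The effect on power is modest: 90.2% at the planned 10% loss and 86.5% at an assumed 20%. The effect on bias is conditional. It needs loss that depends on recovery and differs by arm. Under the mechanism assumed above it runs from about 0.1 points for a nearly even split to 1.6 points for the most extreme one. That part can be modelled; loss driven by the unseen 3-month score cannot be reliably modelled, which is the main reason to prefer collecting the score. The loss rates, splits, weighting and correlations are all assumptions, because the article gives none beyond the 10% allowance.

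**What to change.** Keep clinic completion as the default. Amend Outcome assessment and Missing data so that, when a visit is missed, the DASH and the other self-completed measures (pain, EQ-5D, SF-12, satisfaction, return to work and sport) are obtained by post, telephone or online within a stated window around the visit date. Use the same procedure in both arms and record the mode of completion for each score. Only examination and radiographs then depend on attendance.

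The cost is a minor amendment and a reminder, call or form for the few patients who miss a visit. The sample size, endpoint, treatments and visit schedule do not change. Mixed completion modes are the one drawback, and a sensitivity analysis restricted to clinic-completed scores, or adjusting for mode, would show whether they matter.

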### Randomisation

The study will use a parallel assignment model, with 1:1 allocation of patients into each treatment arm (operative or non-operative). Randomisation will be stratified by patient age (< 65 years old or ≥ 65 years old), to ensure there are approximately equal numbers of younger and older patients in each treatment arm. Using block randomisation with a mixed block size and a 1:1 ratio of operative to non-operative, a computer-generated randomisation schedule was produced by a senior statistician from the local clinical research facility using nQuery Advisor v7.0 software (Statsols, Cork, Ireland). A member of staff independent of the study used this schedule to produce a series of opaque sealed envelopes, each containing a sticker bearing the words ‘operative’ or ‘non-operative’. Once the randomisation envelope is opened, the sticker is placed onto the already-signed consent form to indicate the treatment group allocation.

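### A patient without a 3-month DASH cannot enter the primary test, and the only analytic safeguard is an optional sensitivity analysis with an undefined trigger

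*Protocol article*

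**What the plan says.** In the protocol article, the section Power calculation and statistical analysis compares 3-month DASH between arms with an independent-samples t-test, or a rank test if the data are not normal. It adds: "Data will be analysed on an intention-to-treat basis". An ANCOVA adjusting for pre-injury DASH, age and other prognostic factors is also planned.

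The Missing data section does four things:

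- It says the sample size allows for up to 10% loss at 3 months.
- It expects collection at routine clinic visits to limit missing data.
- It commits to reporting and comparing dropout in each arm.
- For analysis at the primary timepoint it then says only: "If the participant dropout rate at the primary outcome timepoint is substantial, a sensitivity analysis may be performed".

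Scores from the other visits have a different use: "Missing data at other timepoints will be accounted for by plotting a line of best fit". The fitted slopes are then compared between arms. The Discussion states that neither patients nor assessors can be blinded.

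**The concern.** A t-test or rank test has no place for a patient whose 3-month score is missing, and the ANCOVA also needs that score. The slope comparison answers a question about rate of change and does not recover the 3-month difference. As written, the primary result therefore rests on whoever attended at 3 months.

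The safeguard depends on the size of the dropout rate, with no threshold, and would be decided once dropout is known. Bias depends instead on who is lost from each arm. The 10% inflation restores numbers and does nothing for bias. In an open-label trial with all scores collected in clinic, attendance may plausibly depend on both arm and recovery. At stake are the accuracy of the primary estimate, its p value and its confidence interval.

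**Working it through.** **1. The plan's own figure.** Inputs: "using a two-sided *t*-test with 5% significance"; "The minimal clinically important difference in the DASH score is reported to be 10 points"; "the assumed standard deviation is 12 points for both the operative and non-operative groups"; 90% power; 1:1 allocation.

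- Normal formula: n = 2(1.96 + 1.2816)² × 12²/10² = 30.3, so 31 per arm.
- With 10% loss: 31/0.9 = 34.4, so 35 per arm and 70 in all. The stated total is reproduced. (The exact t-test version gives 32, then 36 per arm, or 72.)
- The allowance is 10% of 70 = 7 patients.

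**2. Bias formula.** Let D be the DASH gap between lost patients and completers in the same arm, and let l1 and l2 be the numbers lost. Dropping the lost patients shifts an arm's mean by (l/35) × D. The difference between arms is then biased by

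- D × (l1 − l2)/35 if the same kind of patient is lost in both arms;
- D × (l1 + l2)/35 if one arm loses its worse patients and the other its better ones.

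**3. Size under a simulated mechanism.** Assumptions, not in the documents: between-visit correlation 0.5 or 0.7, and loss probability rising (or falling) exponentially with the standardised 6-week DASH. Inputs from the plan: 35 per arm, SD 12, true difference 10, 7 lost.

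| Split of 7 losses | Complete-case bias (points) | Fisher p for dropout by arm |
|---|---|---|
| 7:0 | 1.1 to 1.7 | 0.011 |
| 5:2, same direction | 0.5 to 0.7 | 0.43 |
| 4:3, same direction | 0.1 to 0.3 | not informative |
| 4:3, opposite directions | 1.1 to 1.6 | not informative |

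A 6:1 split gives Fisher p = 0.11. The standard error at 7:0 is 12 × √(1/28 + 1/35) = 3.04.

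Check against step 2: biases of 1.1 and 1.7 at 7:0 imply D = 1.1 × 35/7 = 5.5 and 1.7 × 35/7 = 8.5. At 5:2 these give 5.5 × 3/35 = 0.47 and 8.5 × 3/35 = 0.73. At 4:3 they give 5.5/35 = 0.16 and 8.5/35 = 0.24. The simulation and the formula agree.

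**4. Effect on the test at 7:0.** Type I error = Φ(−1.96 − b/3.04) + 1 − Φ(1.96 − b/3.04).

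- b = 1.1 gives 6.5%, and b = 1.7 gives 8.7%.
- If the bias runs against a true 10-point difference, power = Φ((10 − b)/3.04 − 1.96). That is 83% at b = 1.1 and 78% at b = 1.7, against 91% with no bias.

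**5. Larger assumed gaps.**

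- D = 12 (one SD): 7:0 gives bias 2.4 and type I error 12.4%; 5:2 gives 1.0 and 6.3%; 4:3 gives 0.3 and 5.1%.
- D = 24, the extreme end: 7:0 gives 4.8 and 35%.
- Cancelling a 10-point effect at 7:0 would need D = 10/(7/35) = 50.

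**6. What the other visits recover.** If loss depends on the 6-week DASH, an estimate using that score leaves bias of at most 0.1, with no larger standard error. If loss depends on the unseen 3-month score itself, 7:0 bias falls only from about 2.2 to between 1.1 and 1.7.

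**The case against.** - **There is a check.** A reader might infer that arm-dependent loss would pass unchecked. The documents do not support that: the Missing data section commits to reporting and comparing dropout by arm, and a 7:0 split would show up. What remains is that the comparison looks at rates only, would probably not flag 6:1 or 5:2, cannot see a difference in reasons for loss, and triggers nothing stated.
- **The trigger may not mean total dropout.** Nothing says that loss within 10% is insubstantial, and 20% loss in one arm could be judged substantial. That is fair. It also shows that the wording does not settle the matter.
- **Complete-case analysis is inferred.** The article does not use the term, and a SAP not shown may name a method. This stands as a limit on the claim. The point rests on what the article does fix: a test that needs the observed score, and a sensitivity analysis made optional.
- **Intention-to-treat may mean analysis by allocated arm.** A t-test respects that, so no breach is claimed.
- **The simulation favours the remedy.** When loss depends on an observed 6-week score, a model using that score must work. This is correct, and it is why step 6 shows the less favourable case and why a sensitivity analysis is needed as well.
- **A 2-week DASH is not established.** The text confirms DASH from 6 weeks to 1 year. The follow-up section mentions only a questionnaire at each visit, and the schedule figure is not shown.

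**Conclusion.** The concern holds in a limited form. At the primary timepoint the stated test can use only observed scores, and the one analytic safeguard is optional and has no defined trigger. Loss related to recovery that differs by arm in rate or reason can bias the result within the 10% allowance.

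Under the simulated mechanisms the bias runs from about 0.1 to 1.7 points, or up to 17% of the 10-point minimal important difference and a little over half a standard error. Larger gaps between lost patients and completers would give more. The correlations, the loss mechanism and the gaps are all assumptions.

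A reader might go further and conclude that the result will be biased or that the trial's answer could be reversed. The documents do not support either. Bias needs informative loss that is unbalanced in number or kind, same-direction 4:3 loss is nearly harmless, and a 10-point effect would survive. The realistic harm is to a borderline result. The change should be made, but the design does not depend on it.

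**What to change.** 1. Estimate the 3-month difference from a mixed model for repeated measures over the DASH visits that the text confirms (6 weeks, 3 months, 6 months, 1 year), adding 2 weeks if it is collected. Include treatment-by-visit terms, pre-injury DASH and the age stratum (under 65, or 65 and over), with unstructured covariance. Multiple imputation by arm using the same variables is an acceptable alternative, and it can also include patients with no follow-up score, whom the mixed model leaves out.
2. Keep the t-test on observed scores as a supportive analysis.
3. Replace the optional sensitivity analysis with one that is always run, whatever the dropout rate. Shift the imputed 3-month scores by 0 to 10 points, separately in each arm, and report where the conclusion changes. For scale, a 10-point shift in 7 of 35 patients moves the difference by 10 × 7/35 = 2 points.
4. Keep the comparison of dropout by arm, and report reasons for loss with it.

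The cost is a few lines of plan text fixed before analysis, some programming, and slightly more model specification than a t-test. No new data, visits or patients are needed, and N stays at 70.
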